## Abstract

**Background:**

Two overweight prevention interventions were developed to be offered by preventive Youth Health Care (YHC) in addition to the currently applied overweight prevention protocol to parents of 0-3 year old children. The two interventions aim to support parents of preschool children to realize healthy child nutrition and activity behaviors of their young child. The aim of this study is to assess the effects of the two overweight prevention interventions with regard to child health behaviors and child Body Mass Index.

**Methods/Design:**

A cluster randomized controlled trial was conducted among parents and their preschool children who attend one of 51 participating YHC teams. The teams were randomly allocated to one of the two intervention groups, or to the control group (care as usual).

The ‘BBOFT+’ intervention focuses on effective child rearing by parents from birth onwards by enlarging parental skills concerning healthy behavioural life-style habits. Parents who are allocated to the ‘E-health4Uth Healthy toddler’ intervention group, at the child age of circa 18 and 24 months old, are invited to complete an online E-health module providing tailored health education regarding healthy child nutrition and activity behaviors. The E-health messages are discussed and reinforced during the subsequent regularly scheduled visits by YHC professionals, and were repeated after 4 weeks.

The primary outcome measures at child age 3 years are: overweight inducing/reducing behaviors, (for ‘BBOFT+’ only) healthy sleep, Body Mass Index and prevalence of overweight and obesity. Secondary outcome measures are attitudes and other cognitive characteristics of the parents regarding the overweight-related behaviors of their child, parenting styles and practices, and health-related quality of life of the children.

**Discussion:**

We hypothesize that the use of the additional interventions will result in a healthier lifestyle of preschool children and an improved BMI and less development of overweight and obesity compared to usual care.

**Trial registration:**

Nederlands Trial Register NTR1831.

## Background

In the Netherlands, a system for monitoring children’s health and development, and for providing health promotion and disease prevention at set ages from birth onwards is available: i.e. preventive Youth Health Care (YHC), which is offered nation-wide and free of charge [1]. Participation is voluntary and the attendance rate is about 95%. During the YHC visits, growth and development of the child are assessed [1,2]. YHC is committed to counsel parents regarding parenting competence, and to promote healthy development and growth for all children [2]. YHC can also support public health strategies that are needed to tackle the problem of the increasing prevalence of childhood overweight and obesity [3,4]. In 2010, the prevalence of overweight (including obesity) in the Netherlands was 13,3% and 14,9% for 2–17 year-old boys and girls respectively. For obesity, this was 1,8% for boys and 2,2% for girls [5].

Consensus regarding overweight prevention in the setting of YHC has been reached and consists of two elements, i.e. a YHC-Overweight detection protocol [6] and a YHC-Overweight prevention protocol [7]. The YHC-Overweight prevention protocol includes (a) a strategy for primary prevention of overweight (i.e. promotion of healthy energy balance-related behaviors in the child population), and (b) a strategy for secondary prevention of overweight (i.e. detection of children with overweight and intensive counseling of these children and their parents).

Based on the YHC-Overweight prevention protocol and an observational study that included 390 families with children aged 0–4 years regarding health behaviors and parents’ views regarding health behaviors of their young children [8], we developed two interventions, i.e. the ‘BBOFT+’ and the ‘E-health4Uth Healthy toddler’ interventions. The ‘BBOFT+’ intervention focusses on effective child rearing by parents from birth onwards by enlarging parental skills concerning healthy behavioural life-style habits of the child. The ‘E-health4Uth Healthy toddler’ intervention consists of an E-health module providing tailored health education regarding healthy child nutrition and activity behaviors, which is combined with face to face counseling by YHC nurses.

The two interventions, ‘BBOFT+’ and ‘E-health4Uth Healthy toddler’ both fit into the YHC Overweight-prevention-protocol. Both interventions aim to promote relevant health behaviors regarding a healthy weight development of young children: breast feeding (only in the ‘BBOFT+’ intervention), daily exercise/outdoor playing, breakfast daily, few sweet drinks, and minimal TV time. Additionally, the ‘BBOFT+’ intervention is designed to promote healthy sleep behaviors of the child. The two interventions are described in detail below.

### Objective

In this study, the effectiveness of the two interventions (‘BBOFT+’ and ‘E-health4Uth Healthy toddler’) that involve primary prevention of overweight and obesity in early childhood is evaluated in comparison with usual care in a cluster randomized controlled trial. In addition, the level of adherence of parents and YHC professionals to the distinct elements of the ‘BBOFT+’ intervention and the ‘E-health4Uth Healthy toddler’ intervention will also be taken into account, as well as how parents appreciate these elements. In this article the design of the evaluation study is described.

### Study hypotheses

The hypotheses of this study are that at the age of three years, children in the two intervention groups will have healthier lifestyles and a more favorable development of BMI, i.e. less development of overweight and obesity, compared to children in the control condition (‘usual care’). In addition, we hypothesize that attitudes and other cognitive characteristics of the parents regarding the overweight-related behaviors of their child, and that parenting styles and practices, and health-related quality of life of the children will be more favorable in the two intervention groups compared to the control condition.

## Methods/Design

### Study design, procedure and participants

The study is a cluster randomized controlled trial (c-RCT) with two intervention conditions and a control condition (‘usual care’). The inclusion of participants is shortly after child birth, with repeated measurements; the last measurements occur at child age of circa 36 months (see Figure 1).

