Secondary outcome measures are attitudes and other cognitive determinants of the parents regarding the health behaviors of their child, parenting styles and practices, and child health-related quality of life: (1) Attitudes, motivation and perceived control among parents regarding the four energy balance-related behaviors [24], (2) General parenting styles and parental practices and rules (these will be measured by Child rearing questionnaire for parents [26] and parenting practices and rules in relation to physical activity and food [27]), (3) Child health-related quality of life and wellbeing (Infant Toddler Quality of Life questionnaire - ITQOL) [24]). Concerning the secondary outcomes it is hypothesized that more favorable attitudes and other determinants of the parents regarding the overweight-related behaviors of their child will be present in each intervention group, compared to the control group. It is hypothesized that general parenting styles are less often restrictive and permissive, and more often authoritative in each intervention group compared to the control group, and that parenting practices and rules in relation to physical activity and food are more favorable in each intervention group, compared to the control group. It is hypothesized that child health-related quality of life and well-being are more favorable in each intervention group, compared to the control group.

We will explore whether one or more of the following variables have an effect on the relationship of interest, and if so, include them in the analyses as confounder: (1) Pregnancy duration and birth weight (from YHC files), (2) Parents’ BMI using self-report (self-report of adult height and weight has proven to be sufficiently accurate for epidemiological research [28]), (3) Parents’ health-related quality of life and wellbeing (SF-12), (4) Age, educational level and ethnic background of the parents.

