### Size of the study and power considerations

Fifty-one YHC teams of ten Youth Health Care providers participate in the study. They invited 3570 parents/children to participate in the study (two intervention groups and one control condition). Taking into account informed consent by 50% and dropout between baseline and follow-up of 30%, we expect complete data of 1250 parents/children at follow-up, equally divided over the two intervention groups and the control group. We assume equal standard deviations in the intervention groups and the control group, an alpha of 0.05 (2-tailed) and power of 0.80. We apply a correction factor to account for the cluster design, assuming an average cluster size of 25 toddlers (1250/51) and an intra-class correlation coefficient of 0.10. For this expected sample size and assumptions, we calculated minimal detectable differences between the intervention groups and the control group at follow-up.

Some illustrations: Regarding the mean number of the reported minutes of playing outside of the children per day, the study can detect a difference between an intervention group and the control group of 15 minutes/day (SD=52 min/day). Regarding the mean consumption of sweet drinks in glasses per day, a difference of 0.4 glasses/day (SD=1.5 glasses/day) can be detected. Regarding the mean number of minutes of TV viewing per day, a difference of 9 minutes/day can be detected (SD=32 minutes/day). BMI at age 36 months old: a difference of 0.38 BMI points between the mean BMI in an intervention group and the mean BMI in the control group can be detected by the study (SD=1.3).

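### Outdoor play and screen time are compared at about 36 months, so the outcome falls in the child's birth season, but no calendar-time term is planned: a cheap loss of precision, not a demonstrated bias

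*Protocol article*

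**What the plan says.** **Timing.** Under Study design, procedure and participants, parents are approached in the second week after birth and "the last measurements occur at child age of circa 36 months". The Measurements section places the outcomes at age 3 years. Questionnaires also go out at inclusion, 6 and 13 months, and using these in the evaluation is optional.

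**Outcomes.** Activity and outdoor play, and time on television, computer and computer games, are among the primary behaviours. Outdoor play is also the first illustration in the power section ("Regarding the mean number of the reported minutes of playing outside of the children per day"), with a detectable difference of 15 min/day and an SD of 52.

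**Covariates.** Measurements introduces its candidate confounders with "We will explore whether one or more of the following variables have an effect on the relationship of interest" and then numbers four groups:
- pregnancy duration and birth weight;
- parental BMI;
- parental quality of life;
- parental age, education and ethnic background.

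Data analyses adds baseline values and any relevant potential confounders to a multilevel model by team. The effect modifiers to be explored are gender, parental education, ethnic background and parental overweight. Calendar time appears in none of these places.

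**Design.** There are 51 teams, 17 per arm, randomised within each of ten organisations. Data collection runs from 2008 to fall 2013. No recruitment window is given for a team or an arm.

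**The concern.** How long a three-year-old plays outside plausibly depends on the time of year, and screen time may move the other way. Because children enter at birth and are assessed at a fixed age, the season of the outcome is set by the date of birth. If a team enrols its families over a few months only, its children are also assessed in a few months of the year, and season becomes a source of variation between teams. Teams are the randomised units, and there are only 17 per arm.

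Nothing else in the planned model is likely to absorb this. A baseline taken at 2 to 4 weeks of age offers no comparable value for a toddler's outdoor play or television time. The 6- and 13-month questionnaires fall at other ages, and the first of them in the opposite season. The team random effect puts seasonal variation into the standard error but does not remove it. At stake is the width of the confidence interval for outdoor play and screen time, and a chance seasonal difference between arms that goes uncorrected.

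**Working it through.** **Inputs from the article** (Size of the study and power considerations; Study design): "an alpha of 0.05 (2-tailed) and power of 0.80"; 1250 complete cases in three equal groups, so n = 1250/3 = 416.7 per arm; 17 teams per arm; ICC 0.10; outdoor play SD 52, so total variance 52² = 2704.

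**Assumptions, not in the article.** Outdoor play follows a yearly sine wave with amplitude A = 10, 20 or 30 min/day either side of the mean. Each team recruits over a window of W months, with windows spread at random over the year.

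**The plan's own figure first.** With z = 1.960 + 0.842 = 2.802 and a design effect of 1 + 24 × 0.10 = 3.4:

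2.802 × 52 × √(3.4 × 2/416.7) = 18.6 min/day.

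The stated 15 is therefore not reproduced. With 625 (1250/2) per arm the same formula gives 15.2. That is a separate matter, but it means the reference value below is about 18.5, not 15. Split into components (between teams 270.4, within teams 2433.6), the formula is

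MDD = 2.802 × √[2 × (between/17 + within/416.7)] = 2.802 × √[2 × (15.91 + 5.84)] = 18.5.

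It differs slightly from 18.6 because the actual mean cluster size is 24.5 rather than 25.

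**Adding season.** A window of W months leaves a team-mean amplitude of A × f, with f = sin(πW/12)/(πW/12). This is 0.900 at W = 3, 0.637 at W = 6 and 0 at W = 12. Then:
- seasonal variance between teams: vb = (A f)²/2;
- total seasonal variance: vt = A²/2;
- SD of the chance arm difference due to season: √(2 vb/17).

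The total variance is held at 2704. Without season in the model, between = 270.4 + vb and within = 2433.6 − vb. With season in the model, between = 270.4 and within = 2433.6 − vt.

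| W (months) | A | vb | SD of chance arm difference | MDD without season | MDD with season | Gain |
|---|---|---|---|---|---|---|
| 3 | 10 | 40.5 | 2.2 | 19.4 | 18.4 | 1.0 |
| 3 | 20 | 162.1 | 4.4 | 22.0 | 18.3 | 3.8 |
| 3 | 30 | 364.8 | 6.5 | 25.8 | 18.0 | 7.8 |
| 6 | 10 | 20.3 | 1.5 | 19.0 | 18.4 | 0.5 |
| 6 | 20 | 81.1 | 3.1 | 20.3 | 18.3 | 2.1 |
| 6 | 30 | 182.4 | 4.6 | 22.4 | 18.0 | 4.4 |
| 12 | 10 | 0 | 0 | 18.5 | 18.4 | 0.05 |
| 12 | 20 | 0 | 0 | 18.5 | 18.3 | 0.2 |
| 12 | 30 | 0 | 0 | 18.5 | 18.0 | 0.5 |

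SDs, MDDs and gains are in min/day; gains are taken before rounding.

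**If the ICC of 0.10 already contains season**, the unadjusted value stays at 18.5. Adjustment at W = 3 then brings it to 17.4 (A = 10) or 13.8 (A = 20). A = 30 is not compatible with that reading, because vb = 364.8 exceeds 270.4. Adjustment helps under either reading.

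**The case against.** **The covariate list is not closed.** The article speaks of exploring variables and of relevant confounders, if any, and an analysis plan that is not shown could add the date of measurement. That is fair, and it is why this is an improvement rather than an error. But the article does name its candidates, in four numbered groups, and none carries calendar time. The point is a useful predictor missing from a stated list, not detail that an article has left out.

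**Season as a property of the team.** A reader might infer this from about 70 invitations per team (3570/51). The article gives no births per team and no recruitment window, and its overall dates, 2008 to fall 2013, do not fix one. With year-round recruitment the team-level link disappears.

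**Systematic bias.** A reader might also infer that the arms started in different months, because BBOFT+ begins at birth after staff training while E-health4Uth begins at 18 months. The article reports no such stagger. It places the instruction meetings before the study start without distinguishing arms. Randomisation within organisations makes season unrelated to arm in expectation. If teams of one organisation recruited over the same months, that stratification would hold the chance imbalance below the SDs shown above.

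**The random effect covers chance differences.** It does so for the validity of the standard error. It neither recovers the lost precision nor corrects an imbalance that has occurred.

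**Measured once.** This is true only of the outcome comparison, because earlier questionnaires exist. They do not adjust the 36-month value for its own season.

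**Conclusion.** The point holds as a matter of precision and chance imbalance. Season of the outcome follows season of birth, two groups of primary behaviours plausibly depend on it, and no calendar-time term is planned.

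For outdoor play, with assumed amplitudes of 10 to 30 min/day, the gain in detectable difference is about 1 to 8 min/day with 3-month team windows and under 1 min/day with 12-month windows. The SD of the chance arm difference is about 2 to 7 min/day in the first case and 0 in the second. Amplitude, window length and random placement of windows are all my assumptions, and the article supports no particular value within these ranges. I have no figure for TV/computer time.

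Adjustment improved precision in every scenario computed. The documents do not support a claim that the contrast between arms is biased.

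**What to change.** Add one sentence to Data analyses: the models of outdoor play/activity and of TV/computer time include season as a prespecified fixed covariate in all arms, either as quarter of the year or as sine and cosine of month. Preferably derive it from the due date of the 36-month assessment (birth date plus 36 months). The intervention cannot affect that date, whereas it could affect when a questionnaire is actually returned. Report the distribution of actual measurement month by arm, which would also show whether the arms were assessed at different times of year. Sweet drinks need not be included, since there is no seasonal argument for them here.

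The cost is 2 degrees of freedom (sine and cosine) or 3 (quarter) per model, one derived variable and no new data.

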**Figure 1 F1:**
[figure not shown]
Flowchart of the design of the study.

Managers of all regional Youth Health Care (YHC) organizations in the Netherlands (n=50) were informed about the study and were invited to participate in the study. Ten YHC organizations volunteered to participate. In total, 51 YHC teams were available to participate in the study (three times seventeen teams). These teams covered both rural and urban regions in the Netherlands. Prior to the start of the study, the researchers arranged meetings to explain the procedure of the study, and to instruct the participating YHC professionals. Within each organization, YHC teams were randomly assigned to either one of the two intervention groups or the control group by a computerized random allocation generator. Data collection started in 2008 and continues until fall 2013.

The Medical Ethical Committee of Erasmus Medical Center has declared that the Medical research Involving Human Subjects Act (also known by the Dutch acronym WMO) does not apply to this study. The Medical Ethical Committee had no objection against the execution of this research proposal (reference number MEC-2008-250).

The study includes parents and their babies/toddlers that belong to one of the participating YHC teams, and who are eligible for the regular YHC visits from birth until age three years. The parents are informed about the study when the YHC nurse visits the parents in the second week after birth. Parents are provided with information about the study, an informed consent form, and a short questionnaire with items on background data (i.e. the baseline questionnaire); the parents were invited to provide written informed consent to participate in the study, and to complete the short questionnaire. The study design and participant flow are shown in Figure 1.

### The ‘BBOFT+’ intervention

The ‘BBOFT+’ intervention intends to promote the key behaviors for the prevention of overweight in children as defined in the YHC-Overweight Prevention Protocol (see Table 1); i.e. breast feeding, and, once applicable, daily exercise/outdoor playing, breakfast daily, few sweet drinks, and minimal TV time. Additionally, the ‘BBOFT+’ intervention is designed to promote healthy sleep behaviors of the child. Parental positive child rearing competences and skills are addressed in this intervention. YHC professionals receive training about child rearing and aspects of the learning theory to be applied in the course of the ‘BBOFT+’ intervention.

**Table 1 T1:** Targets of the ‘BBOFT+’ approach

Enlarging parenting skills is operationalized as:	- Increase children’s self-esteem by spending time with the child, talk and show affection to the child. Regularly interact with a child while it is behaving positive, and talk with children about their activities, cuddle, touch, and hold the child (body contact)
	- Encourage healthy behaviors: reinforce positive behavior by praising the specific behavior
	- Give positive attention: offer non-verbal attention (smiling, touching)
	- Offer attractive activities: play material etc. (age and development phase related)
	- Parent is positive example (modeling)
	- Reinforce spontaneous learning moments
	- Reinforce learning by experience, instruction
Stimulus control	- Basic rules and regulations (age en development phase related)
	- Direct intervention when child is misbehaving
	- Clear instructions in a quiet way
Operant conditioning	- Misbehavior will be related to direct consequence
	- Time out
	- Positive reinforcement
	- Child rearing: warm, positive, and also monitoring and setting borders
	- Grandparent’s behavior (no spoiling)
Optimize nutrition is operationalized as:	- Establishing eating routine (0–9 months regularity and stimulus reduction)
	- > 6 months specific times for meals and snacks (stimulus control)
	- Prevention of introduction of extra foods (unhealthy snack foods, take away, sugar drinks)
	- Provision of healthy alternatives
Optimize physical activity is operationalized as:	- Prevention of sedentary activities (TV etc.)
	- Improve daily physical activity (daily walk, play-pen, tummy time, play outside etc.)
Optimize sleep duration and sleep behavior is operationalized as:	- Optimal sleep duration per day
	- Hours an infant can remain awake
	- Time the child needs to fall asleep
	- Number of times the child wakes up during the night

The YHC nurses and physicians receive a small, calendar-like booklet, with on the front side pictures of infants and toddlers who show the desired healthy behaviors and on the backside items about the behavioral items to put forward by YHC professional. This booklet is placed on the desk, with the pictures to the parents and the text to the health care worker; the purpose is to support the counseling, especially for those who are low- or illiterate. The items are adapted to the developmental phase of the child and concern: (1) So-called ‘authoritative’ child rearing and parenting skills, (2) Healthy food and feeding behaviors, (3) Daily exercise and outside playing, (4) Minimal television and computer use, (5) Adequate sleep duration and healthy sleep behaviors (see Table 2). All items are emphatically and positively formulated.

**Table 2 T2:** Schematic overview of the ‘BBOFT+’ intervention

Feeding	• Breastfeeding	± 2 weeks
	• Variation in maternal food	± 1,2 months
	• No extra bottle when breast feeding	± 2 weeks, ± 2 months
	• Left overs allowed in bottle	± 2 weeks, ± 2 months
	• No extra supplements in bottle	± 1 month
	• Level spoon for bottle feeding	± 1 month
	• Do not reward every cry or fuss with feeding	± 2 months
	• Eat in a social setting (not in front of TV)	± 1 month
	• Accustom to different structures	± 3 months
	• Accustom to different tastes	± 4, 71/2 months
	• Difference home-made food and food from jars	± 6 months
	• Eating at the same time at the table	± 4,6, 71/2 months
	• No TV watching while eating	± 9,11,18,24,36 months
	• Positive atmosphere at the table	± 9,11,18,36 months
	• Child may eat less or more in this phase	± 14,24 months
		± 14,24 months
Space to move and play with pleasure	• Tummy time	± 2 weeks, 1,2,3,4,6 months
	• Car seat is for transport	± 4 months
	• Not too long in rocking chair	± 4 months
	• Get baby out of playpen before it starts to cry	± 4 months
	• The playpen is a safe a nice place to play	± 6, 71/2,11 months
	• The playpen is a stimulant for motoric development	± 6, 71/2,11 months
	• Let the toddler walk itself when/where possible	± 14,18,24,36 months
Daily outside		± 2 weeks, 1,2,3,6,9,11,14,18 months
Sleep	• Duration (sleeping/awake)	± 2 weeks, 1,2,3,4,6,71/2,9,11, 18,24,36 months
	• Put the baby to sleep awake	± 2,3, 71/2 months
	• Sleep in afternoon gradually reducing	± 71/2 months
	• Late feeding in the evening not necessary anymore	± 71/2,9,11,18 months
	• Children like rituals when going to bed	± 9,11,24,36 months
	• A bottle “to fall asleep” is not necessary	± 9,11,14 months
	• Bedtime	± 11,18,24,36 months
Regularity, uniformity in daily care and reduction of stimuli	• Fixed order: sleeping, feeding, playing, getting tired, bring to bed awake	± 1,2,11,14,18 months
	• Crying increases till 6-8 weeks, and decreases after 8 week	± 1 months
	• Play in playpen, transport in car seat	± 2 months
Parenting	• Role/influence grandparents	± 2,71/2,18,36 months
	• Children need warmth, love and safety	± 2,3,71/2 months
	• Sensitive and warm parenting and at the same time restriction	± 71/2,9,14,18,24,36 months
	• Sweets/food not to be used as reinforcer of behavior	± 71/2,9,14,18 months
	• Parenting style	± 9,24 months
	• Children like predictability	± 14 months
	• Screen/food not to be used as reinforcer of behavior	± 24,36 months
Screen	• A baby and TV watching don’t match	± 3,4,6,71/2,9 months
	• No television in bedroom of the child	± 11,14,18,24,36 months
	• Watch TV together	± 14 months
	• Watch TV/play computer together, not longer than 1 hour, daily	± 24,36 months
Drinking	• When thirsty, offer water	± 4,6,9,11,18,24 months
Snack	• Water and diluted fruit juice or tea (no sugar), and bread crust or cracker	± 9,11 months

Parents who are allocated to a ‘BBOFT+’ team receive advice and care during the regularly scheduled visits, i.e. 8 to 11 contacts in the first year, and 5 contacts in total in the second and third year of life. BBOFT+ YHC nurses and physicians apply the intervention during each contact with parents. Promotion of continued breastfeeding has a specific context and is mainly limited to the first year of life. The other behaviors and child-rearing issues receive attention from birth onwards.

The rationale of the intervention is that parents will enlarge their parenting skills and will increase children’s self-esteem, and will encourage healthy child behaviors by setting a good example and using praise and reward, and by managing problem behaviors of their child by setting ground rules, clear instructions and the use of consistent measures [9,10].

In the ‘BBOFT+’ intervention, YHC nurses have to be able to disseminate knowledge; i.e., they need to have the skills to coach parents in achieving competent parenting. In this intervention, behavioral goals are set out: these goals are partially derived from an earlier study [8]. The intervention targets parenting skills in the context of everyday, naturally occurring examples. Specific anticipating parenting education is given during the standard YHC visits. Parents are taught the principles of stimulus control, modeling and operant conditioning. The ‘BBOFT+’ intervention includes targeted education that anticipates on common problems, and explains the basics of stimulus control and classical conditioning in order to enable parents to create the conditions that stimulate the desired behavior in the child (Table 1).

The start of the intervention focuses on the transition to the phase of a young parent; during this phase, parents are expected to be receptive to suggested behavior changes and new knowledge. The BBOFT+ intervention acknowledges the possibility of enhancing self-control of the child by a so-called ‘authoritative’ parenting style. Modeling, stimulus control, and operant conditioning such as intermittent confirmation are used during these contacts [11]. In BBOFT+, social learning principles are applied consisting of both classic and operant conditioning. For instance that specific behavior is caused by antecedent factors, that one should try to intervene before the unwanted behavior occurs, and that one should create conditions suitable for positive behavior. Parents learn that it is important to set clear boundaries, and to have unambiguous rules. They receive suggestions to help structuring time and space, to introduce ground rules, and to state these rules clearly and consistently. Couples should collaborate as a team in defining the rules and applying them consistently. By controlling the stimuli in this manner, disruptive behavior can be avoided according to this approach [12]. BBOFT+ supports the creation of ‘authoritative’ environments characterized by expression of warmth and emotional support, together with using clear, bidirectional communication [13]. The literature shows that an authoritative child rearing style is related to a lower risk of overweight and obesity [14].

In the BBOFT+ intervention teams, the YHC professionals are offered training to provide them with knowledge, skills and explicit guidelines on child rearing; they are educated about aspects of the learning theory. The introductory training of the ‘BBOFT+’ intervention teams consists of 1 session of 4 hours. After a year, this training is repeated to motivate the ‘BBOFT+’ intervention teams and to ensure proper compliance to the protocol of the intervention (see Table 2). The second training session focuses on the developmental stage of the children at that moment. The trainer of the intervention team is a psychotherapist, educated in behavioral therapy (MH).

